These results, while encouraging, are also limited by various factors including small sample size, single centre administration and sample composition predominately limited to people with RRMS. Whether people with progressive disease will derive the same benefits from these interventions is therefore not known, although a single study suggests that improvement in memory may be possible with CR [4]. The gaps in our knowledge therefore suggest a number of complementary ways forward. Multisite replication of these preliminary, promising findings is a good place to start. However, as people with progressive MS constantly remind us, time is short. This suggests that an additional effort is required, a bolder approach, one that combines more than one intervention with the aim of producing synergistic effects, an improvement in one area boosting the putative benefits of therapy in another, the overall outcome exceeding the sum of the individual treatments. Such an approach often reflects the clinical reality of PMS where multiple neurological difficulties rather than an isolated problem must be addressed simultaneously. While a powered joint CR and exercise clinical trial has yet to be done in people with MS of any disease course there is tentative evidence from three small studies in people with RRMS that this approach may be more beneficial than either intervention alone [15–17]. Thus, a methodologically rigorous, well-powered study is needed now in PMS specifically in an effort to inform clinical practice. It is only through such a study that we can ensure that final conclusions and recommendations are not limited by sample size, generalizability or methodological concerns.

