### Aim, design and setting of the study

The study has the following primary aims:
To assess whether CR and exercise (EX) in combination have beneficial synergistic effects in the treatment of impaired processing speed in people with PMS.To determine whether CR and EX are individually effective treatments for impaired processing speed in people with PMS.

Secondary aims:
To assess the everyday life impact of cognitive and/or physical changes after the different rehabilitation interventions.To assess brain functional and structural substrates of cognitive changes after the different rehabilitation interventions.

This study is a multicenter, multi-arm, randomized, double-blinded, sham-controlled trial that includes follow up periods of 12- and 24 weeks (+/− 2 weeks) post randomization. As depicted in Fig. 1, after the baseline assessment each participant will be randomized to one of four arms with different combinations of CR and EX and their respective shams (−S). That is: CR + EX; EX + CR-S; EX-S + CR; EX-S + CR-S.

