
We propose to treat four groups of participants as noted above. We estimated our sample size using a standard 1-factor analysis of variance approach with a Type I error set at 5%. We computed the sample size necessary to achieve 80% power for such a design assuming conservative changes. For simplicity we used 4 points for the combined treatments, *assuming* that we want to demonstrate a clinically meaningful difference on average and that the two interventions are additive; 4 more correct answers has been suggested by the FDA as a meaningful change [37]*.* We also assumed a change of 2 answers for each of the single interventions and 0 for the sham group [83]. (Note *again* that the learning curve and practice effects will contribute equally to each group and the results shown below are the same if we had chosen 6, 4, 4, 2 *or* other combinations with the same relative spread to accommodate the practice effects, etc.)

Table 6 shows that with 90 participants per treatment group at the time of analysis, there is over 80% power to detect differences as specified (4,2,2,0) across the four groups when the standard deviation of the change is 8 points and the overall Type I error to detect any mean differences is 0.05.

**Table 6 Tab6:** Power for 4 group Analysis of Variance with mean changes in the SDMT of 4 more correct for the combined group; 2 more correct for each of the single intervention groups and 0 change for the Sham Group

**Power**	**n**	**Total N**
0.52751	50.00	200
0.57247	55.00	220
0.61476	60.00	240
0.65423	65.00	260
0.69081	70.00	280
0.72449	75.00	300
0.75533	80.00	320
0.78341	85.00	340
0.80885	90.00	360
0.83179	95.00	380
0.85239	100.00	400

In order to assess the sensitivity of these calculations to assumptions, we conducted a few additional patterns of response and standard deviations. Clearly for any standard deviation smaller than 8, we have more power. For example, if the standard deviation of the change were 7 instead of 8, the power is 91% with 90 patients per group and 81% with 70 per treatment group. If the treatment difference pattern is 4,1,1,0; the power is 86% with four groups assuming a standard deviation of 8.

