### Statistical analyses

The statistical analyses will begin with descriptive analyses of baseline characteristics (age, sex, disease duration, EDSS, other physiologic parameters at baseline and over time, medications, etc.), by treatment allocation ((1) EX + CR, (2) EX + CR-S (3) EX-S + CR or (4) EX-S + CR-S). Continuous variables will be summarized using the statistics mean, median, SD, minimum and maximum. Categorical variables will be summarized with frequency counts and percentages. During the trial, drop-outs and losses to follow-up will be compared between groups to ensure high follow-up rates and comparability and that no particular demographic or site is differentially dropping out of one treatment group. The currently supported version of SAS software will be used to perform all data analyses.

Summary tables will indicate the number of subjects with complete data for each measurement, event or outcome. All analyses will be based on available data, unless otherwise stated, and the intent-to-treat principle. Secondary analyses will examine the per protocol analysis population. All confidence intervals will be two-sided and will use 95% confidence levels. Any analyses requiring significance testing will use a two-sided test at the 5% significance level, unless otherwise specified.

Differences in baseline characteristics between groups will be examined in continuous variables, such as age and disease duration using an ANOVA and categorical variables using a Chi-square tests of association. Informative censoring will be examined with potentially biased imputation and non-informative censoring as well as missing-at random assumptions using multiple imputation to provide sensitivity analyses of the primary results.

The primary analysis will utilize an ANOVA and include an interaction term for the combined treatments. A priori contrasts (stated above in the hypothesis section) will be conducted if the overall test of differences amongst the treatment groups achieves statistical significance. For the pairwise comparisons Dunnett’s test will be used to preserve the Type I error rate. Additional analyses will be conducted as sensitivity analyses using Analysis of Covariance (ANCOVA). These will include site, gender, age and other covariates that may be seen to differ amongst the groups at baseline. Multiple imputation will be used to assess the sensitivity of the primary results to dropouts.

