The imaging component to our study broadens the scope of our inquiry. MRI techniques are currently being applied to investigate mechanisms related to structural and functional brain plasticity in healthy individuals following training and in neurologically impaired individuals following spontaneous recovery and after rehabilitation interventions. Several authors have used fMRI during active tasks or at rest to evaluate the effects of motor [87, 88] and cognitive [18, 36, 89–92] rehabilitation in MS patients. All of these studies have demonstrated that a modulation of function in brain regions have a crucial role in the trained function which occurs in MS after rehabilitation and is associated with clinical improvement. Whether such changes are possible in people with PMS, is not yet known. Our study therefore has the potential to address the dearth of data in this population and shed light on the degree to which neural plasticity is retained in the context of a progressive disease course.

The impact of cognitive dysfunction in the lives of people with MS is considerable. It is associated with difficulties finding and sustaining employment, maintaining intimate relationships and friendships, pursuing leisure activities and managing basic activities of daily living [93]. Given that we have chosen a primary outcome measure, namely the SDMT, in which a 10% (or 4-point) change over time is known to be clinically significant, should our interventions achieve this threshold, they will acquire the imprimatur of an elusive ecological validity. Moreover, the multinational composition of the research teams all pursuing a shared methodology has the potential to demonstrate that the chosen interventions can transcend language, cultural and indeed institutional barriers that make it difficult to extrapolate results from only a single centre.

The study is expected to conclude by the end of 2022. With a robust sample size that ensures adequate statistical power, the findings, if positive, have the potential to guide clinically meaningful interventions for people with PMS who struggle with all the functional limitations associated with slowed processing speed.

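### The 80.9% power is for the overall four-group test under additive means, not for either primary aim (synergy, or the individual effects of CR and EX), and no reading of either aim reaches 80% on the protocol's planning effects

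*Protocol article*

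**What the plan says.** The section on aim, design and setting gives two primary aims. The first is "To assess whether CR and exercise (EX) in combination have beneficial synergistic effects in the treatment of impaired processing speed"; the second is "To determine whether CR and EX are individually effective treatments for impaired processing speed". The Background explains synergy as "the overall outcome exceeding the sum of the individual treatments", which is more than additivity. The Background of the abstract words the hypothesis more loosely: the combination should do better than either treatment given alone.

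The Power analysis section sizes the trial on a one-factor, four-group ANOVA at 5%. Mean SDMT changes are 4 (combined), 2 and 2 (single treatments) and 0 (double sham), on the assumption "that we want to demonstrate a clinically meaningful difference on average and that the two interventions are additive". Table 6 gives 0.80885 at 90 per arm for an SD of change of 8. The sensitivity patterns are 4,1,1,0 (86%) and 3,2,1,0 (59% at SD 8, 71% at SD 7).

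Under Statistical analyses, "The primary analysis will utilize an ANOVA and include an interaction term for the combined treatments". A priori contrasts follow only if the overall test is significant, and pairwise comparisons use Dunnett's test. "Any analyses requiring significance testing will use a two-sided test at the 5% significance level" unless otherwise specified. The Discussion closes its case with "With a robust sample size that ensures adequate statistical power", and the abstract's Discussion also calls the sample robustly powered. Neither statement is limited to the overall test.

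**The concern.** Rejecting the hypothesis that four means are equal shows that some arms differ. It does not show that the combination exceeds the sum of its parts, or that CR or EX works alone. The planning means set the quantity behind aim 1 to zero, and no power is given for the interaction or for any single-treatment comparison.

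Both primary conclusions are at stake. A non-significant interaction, or a non-significant single-treatment result, from a trial described as adequately powered invites the reading that the effect is absent. In the other direction, a significant overall test or a combined arm better than double sham could be reported as synergy, which it is not.

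**Working it through.** **Inputs (Power analysis and Statistical analyses sections).** 90 analysed per arm, four equal arms, SD of change 8 (7 as the protocol's alternative), two-sided 5%, error df 4 × 89 = 356, critical t = 1.967.

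**1. Reproducing the protocol's figure.** For the overall F test, λ = n·Σ(μᵢ − mean)²/SD².
- 4,2,2,0: mean 2, Σ = 4 + 0 + 0 + 4 = 8, λ = 90 × 8/64 = 11.25. Noncentral F (3, 356) gives 0.80885, as in Table 6. All eleven rows of the table reproduce.
- 4,1,1,0: Σ = 6.25 + 0.25 + 0.25 + 2.25 = 9, λ = 12.66, power 85.7% (protocol: 86%).
- 3,2,1,0: Σ = 5, λ = 7.03, power 58.6% (protocol: 59%).

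The table is arithmetically sound, and every power figure in the section is for the overall test.

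**2. What drives it.** Combined v double sham: SE = 8·√(2/90) = 1.193; 4/1.193 = 3.35; power 92% unadjusted, 84% with Dunnett.

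**3. Aim 1 as the interaction** (combined − EX alone − CR alone + double sham). SE = 8·√(4/90) = 1.687.

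| Pattern | Interaction | Power, SD 8 | Power, SD 7 |
|---|---|---|---|
| 4,2,2,0 | 0 | none to detect | none to detect |
| 3,2,1,0 | 3 − 2 − 1 + 0 = 0 | none to detect | none to detect |
| 4,1,1,0 | 4 − 1 − 1 + 0 = 2 | 22% | 27% |
| 4,0,0,0 (illustration, not in the protocol) | 4 | 66% | 77% |

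The interaction detectable with 80% power is (1.960 + 0.842) × 1.687 ≈ 4.7 points at SD 8, and about 4.1 at SD 7. The expected 95% CI half-width at SD 8 is 1.967 × 1.687 ≈ 3.3 points.

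**4. Aim 1 on the abstract's looser wording.** Under 4,2,2,0 the combination exceeds each single treatment by 2 points. The probability that both comparisons are significant, unadjusted, is about 23% by simulation at SD 8.

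**5. Aim 2, a 2-point effect of each treatment.**

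| Comparison | SE at SD 8 | Power, SD 8 | Power, SD 7 |
|---|---|---|---|
| Single v double sham, Dunnett (three comparisons with double sham, critical value about 2.36, simulated) | 1.193 | 25% | 33% |
| Single v double sham, unadjusted | 1.193 | 39% | 48% |
| Factorial main effect, 180 v 180 | 8·√(1/90) = 0.843 | 66% | 77% |

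Requiring a significant overall test first lowers the SD 8 figures slightly: main effect 62%, unadjusted single v double sham 37%.

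**The case against.** Several points on the other side have force.

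- **The section discloses its hypothesis.** It names a one-factor ANOVA, speaks of detecting any mean differences, ties ample power to its assumptions and reports the unfavourable 59% and 71%. A careful reader can see that 80.9% is overall-test power. This stands for the Power analysis section, but not for the abstract or the Discussion, where the limit disappears.
- **Not every pattern is additive.** The 4,1,1,0 pattern has a 2-point interaction. That is correct, but its 86% is again for the overall test; interaction power is 22%.
- **Aim 2 need not be single v double sham.** A two-factor ANOVA with an interaction term also carries the main effects, with 66% power at SD 8 and 77% at SD 7. This stands, and it is why the range must include them. The Dunnett figure also assumes that double sham is the reference, which the article does not state.
- **Aim 1 is worded in two ways.** This also stands, but the looser wording gives 23%, so it does not rescue the power claim.
- **The detail could be left to an analysis plan.** Reporting detail could. A complete power section beside an unqualified statement of adequate power is a matter for this document.

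Two stronger readings are tempting. A reader might infer that power for synergy is 5%. Under 4,2,2,0 there is no synergy, so 5% is the type I error rate and not a power. A reader might also infer that the design could never show synergy. A 4-point interaction would have 66% to 77% power at SD 8 to 7, so the accurate statement is that only a large synergy is detectable with good probability.

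**Conclusion.** The mismatch is real. The trial is sized on a test that answers neither primary aim, under means that contain no synergy, and the general statements of adequate power do not carry over to the aims. At SD 8, 90 analysed per arm and two-sided 5%, 80% power for synergy needs about 4.7 points, more than the 4 points planned for the whole combined effect. Individual effects of 2 points have 25% to 66% power, depending on the comparison chosen. At SD 7 that range is 33% to 77%, still below 80%.

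The figures rest on the protocol's own SD and effect sizes, equal arms with no shortfall from 90, and double sham as the Dunnett reference. They do not show an error in Table 6, which is correct for what it computes.

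**What to change.** 1. In the Power analysis section, state that 80.9% applies to the overall test only, and add the power or detectable effect for each primary aim from the tables above.
2. Limit the statements of robust or adequate power in the abstract and the Discussion accordingly.
3. Define aim 1 as the interaction contrast, align the abstract's hypothesis with it, and report the estimate with its 95% CI. State that a non-significant interaction with a half-width of about 3.3 points is not evidence against synergy, and that combined better than sham, or better than a single treatment, is not synergy.
4. For aim 2, use the factorial main effects (180 v 180), which fit the plan's own additivity assumption, with the simple effects against double sham shown beside them.

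The cost is a change of protocol and analysis-plan wording and a less favourable stated power. Main effects must be read alongside the interaction, because under a real interaction they average over different single and combined effects. No extra patients are needed.

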**Methods:**

This study is a multisite, randomized, double-blinded, sham controlled clinical trial of CR and aerobic exercise. Three hundred and sixty subjects from 11 sites will be randomly assigned into one of four groups: CR plus aerobic exercise; CR plus sham exercise; CR sham plus aerobic exercise and CR sham plus sham exercise. Subjects will participate in the assigned treatments for 12 weeks, twice a week.

All subjects will have a cognitive and physical assessment at baseline, 12 weeks and 24 weeks. In an embedded sub-study, approximately 30% of subjects will undergo structural and functional MRI to investigate the neural mechanisms underlying the behavioral response. The primary outcome is the Symbol Digit Modalities Test (SDMT) measuring PS. Secondary outcome measures include: indices of verbal and non-verbal memory, depression, walking speed and a dual cognitive-motor task and MRI.

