### Study status

By March 2020, a total of 135 participants have been randomized into the study. Of these, 40 are now in the intervention phase, 90 have completed the immediate follow up, 63 have completed the 3-month follow up and 37 have completed the 6-month follow up.

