#### Brain MRI protocol

Brain MRI scans will be obtained using 3.0 Tesla scanners. Budgetary constraints dictate that the MRI is obtained in one third of the sample (i.e. 120 subjects divided equally (*n* = 30) between the four treatment arms). The following sequences will be collected at baseline, termination of the interventions and after 24 weeks of follow up, following a standardized protocol of acquisition and careful guidelines for patients repositioning: axial T2 weighted Turbo Spin Echo (TSE); axial FLAIR; high resolution 3D sagittal T1-weighted sequence; axial DT sequence (55 contiguous, 2.5 mm thick, slices, #DW direction = 64) and T2*-weighted single-shot echo-planar imaging (EPI) during and active cognitive fMRI task and at rest.

For active fMRI, the Go/No-go task will be administered using a block-design, as previously described [66]. Reaction times, omission errors (no response although required), commission errors (false response without adequate cue), and the proportion of correct responses will be recorded using a response-box. Before imaging, participants will be familiarized with the paradigm. The fMRI Go/no-Go paradigm has been used both in cross-sectional [67] and longitudinal [68] studies of people with MS. Notably, a longitudinal (median follow up 20 months) neuropsychological and fMRI evaluation detected significant correlations between worsening of SDMT performances and modification of activation during the Go/no-Go task in several supra- and infratentorial brain regions [68]. Most importantly, the Go/no-Go task has already been validated for multicentric acquisition [66]. During resting state (RS) fMRI, subjects will be instructed to remain motionless, to close their eyes and not to think about anything in particular. Movements will be minimized using foam padding and ear blocks.

The total duration of MRI acquisition (structural plus functional MRI) will be approximately 50 min.

MRI analysis: MRI data acquired for the study will be analyzed centrally at one Neuroimaging Research Unit (Hospital San Raffaele, Milan, Italy).

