If the change is less in the combined treatment group, and the pattern is say 3,2,1,0 and a standard deviation of the change is 8, the power is 59%. If the pattern is 3,2,1,0 and the standard deviation of the change is 7, then the power is 71%. Thus, the power is reasonably high for a variety of the patterns. Obviously increasing the sample size in each treatment group increases the power, but we will increase the number recruited and randomized to account for potential dropouts, thus should have ample power under these assumptions.

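### The figure 360 is both the number to be randomised and the number needed at analysis, so the stated power over 80% (SD 8) leaves room for only about 2% attrition

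*Protocol article*

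**What the plan says.** - Protocol article, Power analysis: the sample size comes from a one-factor ANOVA on four groups with an 80% power target and "the overall Type I error to detect any mean differences is 0.05". For mean SDMT changes of 4, 2, 2 and 0 and a change SD of 8, power exceeds 80% "with 90 participants per treatment group at the time of analysis". The Table 6 row is 0.80885 for 90 per group, 360 in total.
- Protocol article, abstract, Methods: "Three hundred and sixty subjects from 11 sites will be randomly assigned into one of four groups".
- Protocol article, Brain MRI protocol: imaging covers "one third of the sample (i.e. 120 subjects divided equally" across the four arms, 30 in each. That again makes the whole sample 360.
- Protocol article, end of Power analysis: "we will increase the number recruited and randomized to account for potential dropouts". The text then concludes that power should be ample. It gives no attrition rate and no enlarged total.
- Protocol article, Statistical analyses: analyses use available data under intent to treat. Multiple imputation serves as a sensitivity analysis for dropouts.

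**The concern.** One number is doing two jobs. Table 6 needs 360 people with a 12-week SDMT change, and the abstract says 360 people will be randomised. Because the primary analysis uses available data, each participant without that change score reduces the analysed number. The article expects dropouts, since it promises extra randomisation to cover them, but the only randomisation total it prints contains no such allowance. A reader who takes the abstract's 360 together with the power over 80% would credit the trial with a property that the stated size delivers only if nearly everyone is retained. At SD 8 the margin above the target is 0.9 percentage points (80.9 minus 80), so modest attrition uses it up.

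**Working it through.** **Inputs**
- Four groups, one-factor ANOVA, alpha 0.05, 80% power target, mean changes 4,2,2,0 and change SD 8 (Power analysis).
- 360 randomised (abstract), taken as 90 per arm.
- Attrition rate d: not stated. The values 5%, 10%, 15% and 20% are my assumptions.
- Alternative SDs, both from the Power analysis section: 7, used in its sensitivity figures, and 7.6, derived there from a cross-sectional SD of 12 and a correlation of 0.80 (12 × √(2 × 0.20) = 7.59).

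**Formula.** Power = P(F > critical F), where F is noncentral with 3 and 4n − 4 degrees of freedom and noncentrality λ = n × Σ(μᵢ − μ̄)² / SD². The mean of 4,2,2,0 is 2, so Σ(μᵢ − μ̄)² = 4 + 0 + 0 + 4 = 8.

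**Reproducing the plan.** With n = 90 and SD 8, λ = 90 × 8 / 64 = 11.25 on 3 and 356 degrees of freedom. Power is 0.80885, exactly the Table 6 entry. All 11 rows of Table 6 reproduce to five decimals, so the table itself is correct.

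**How much loss the 360 can absorb at SD 8**

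| Analysed in total | Per arm | Power |
|---|---|---|
| 360 | 90 | 80.9% |
| 356 | 89 | 80.4% |
| 353 | 88.25 (average) | 80.0% |
| 352 | 88 | 79.9% |

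The target survives about 7 losses (7/360 = 1.9%) and is missed at 8.

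**Power from 360 randomised**, with n per arm = 90 × (1 − d):

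| Assumed loss | n per arm | SD 8 | SD 7.6 | SD 7 |
|---|---|---|---|---|
| 0% | 90 | 80.9% | 85.1% | 90.8% |
| 5% | 85.5 | 78.6% | 83.0% | 89.1% |
| 10% | 81 | 76.1% | 80.7% | 87.3% |
| 15% | 76.5 | 73.4% | 78.2% | 85.1% |
| 20% | 72 | 70.5% | 75.3% | 82.6% |

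As a worked case, 10% loss at SD 8 gives λ = 81 × 8 / 64 = 10.125 and power 76.1%. The plan's own table shows the same without recalculation: 0.78341 at 340 analysed and 0.75533 at 320.

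**What keeping 360 analysed would imply.** The number randomised would be 360/(1 − d): 379, 400, 424 and 450 at 5%, 10%, 15% and 20% loss. None of these appears in the article as a number to be randomised.

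**The case against.** **The power statement is conditional, and correct as written.** It refers to participants at the time of analysis, and the same section commits to randomising more. Read alone, that section separates the two numbers properly. This stands. It means that the plan does not ignore dropout and that Table 6 contains no arithmetic error. It does not remove the conflict with the abstract, which fixes the randomised number at 360.

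**An article may leave the attrition rate to the full protocol.** Its absence alone would be no finding. The point is that the article prints a randomised total, an analysed total and a promise that the first exceeds the second, and the two totals are equal.

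**The MRI figures do not settle the total.** The abstract says that about 30% will be scanned; 120/0.30 would be 400, and 30% of 360 is 108. This is fair, so the MRI section is supporting evidence only. The point rests on the abstract.

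**SD 8 may be high.** The plan says so, and the table shows that the shortfall shrinks at 7.6 and disappears over this range at 7. Those results belong beside the SD 8 figures. But SD 8 is the basis of the headline claim. The progressive-cohort SDs that the plan cites (13.96 to 15.24) give change SDs of 8.8 to 9.6 at a correlation of 0.80 (multiply by √0.40 = 0.632), so the plan's inputs do not all point downwards.

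**Two stronger readings that the article does not support.** A reader might infer that the design misses 80% as soon as anyone drops out; it does not, because 356 analysed still gives 80.4%. A reader might also take an attrition rate from the Study status section: 135 randomised, less 40 in the intervention phase and 90 with immediate follow-up, leaves 5, or 5.3% of the 95 not in the intervention phase. That section does not say whether those 5 withdrew, had yet to start or were awaiting assessment, so it establishes no rate.

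**Conclusion.** The concern holds as an unreconciled inconsistency with a consequence for power. The randomised number in the abstract, the analysed number behind Table 6 and the promise of extra randomisation agree only with essentially no attrition. At the plan's pattern and SD of 8, the 80% target is lost once losses exceed about 2%, and the shortfall is about 4 percentage points at 10% loss and 9 to 10 at 20%. At SD 7.6 the target is just kept at 10% loss and missed at 15%; at SD 7 it is kept at 20%. These figures assume equal arms, equal attrition across arms and an available-data analysis in which dropouts contribute no change score. The attrition rates are assumed. If the sponsor does intend to randomise more than 360, the shortfall may not arise, and the error is then the 360 in the abstract.

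**What to change.** Reconcile the abstract with the Power analysis section in one of two ways.

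1. If 360 is the randomised total, restate power for 360 randomised at a named, assumed attrition rate: for example, 76% at 10% loss with SD 8, with 81% at SD 7.6 and 87% at SD 7 alongside. Qualify the conclusion that power is ample, and align the closing Discussion statement about adequate power. Remove the promise of extra randomisation, or mark it as not reflected in the 360.
2. If the sponsor already plans to randomise more than 360, put that number in the abstract, with the attrition rate behind it, and adjust the one-third MRI statement to match.

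Either is a change of wording and one or two figures. The first needs no additional participants; its cost is a less favourable power figure at SD 8. The point does not require the sponsor to enlarge the trial.
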